### Secondary objectives

The study aims to assess the effects of an LED and physical activity ILI on other important diabetes outcomes. Secondary outcomes of interest will include body composition and energy expenditure (measured by bioimpedance and indirect calorimetry) and weight loss maintenance, markers of diabetes improvement (HbA1c; measured at a centralised laboratory using turbidimetric inhibition immunoassay for haemolyzed whole blood in ROCHE COBAS 6000c Module), insulin sensitivity/resistance (homeostatic model assessment, HOMA), glucose homeostasis (continuous glucose monitoring system, CGMS) [69], cardiovascular health and risk (blood pressure, arterial stiffness, and endothelial function [70]), impact on diabetes complications (nephropathy, neuropathy, and retinopathy) and liver function tests; steatosis (Fibroscan)), changes in physical activity (measured by questionnaire (International Physical Activity Questionnaire IPAQ and Sedentariness Questionnaire, SIT-Q-7-D [71])] and accelerometry (GT3X) [72]), quality of life (Impact of Weight on Quality of Life (IWQoL-Lite) [73] and EQ-5D questionnaires), and mental health (Hospital Anxiety and Depression Scale (HADS) [4, 74]). Furthermore, the study will investigate any side effects and adverse outcomes of the intervention. Biological samples will be collected for metabolomics, proteomics, non-coding RNA, and microbiome. Fasted venous blood samples will be collected by trained phlebotomists.

### Outcome measures

Table 1 lists key outcome measures and instruments (validated for the study population) used for their measurement.

**Table 1 Tab1:** Key measures and instruments

Key Measures	Instruments	Notes
Body weight and composition	TANITA scales BC420MA	Body weight, and bioimpedance for body composition.
Height	Stadiometer SECA 123	
HbA1c	Turbidimetric inhibition immunoassay for haemolysed whole blood in ROCHE COBAS 6000c Module	Measured at a central laboratory.
Continuous Glucose Monitoring	iPro2 Professional CGM system (Medtronic MiniMed)	Continuous glucose monitoring system (CGMS) will be used for 7 consecutive days.
Quality of Life	1. EQ-5D-5 L 2. IWQOL-LITE	1. EQ-5D-5 L comprises of five dimensions: mobility, self-care, usual activities, pain/discomfort and anxiety/depression. Each dimension has five levels: no problems, slight problems, moderate problems, severe problems and extreme problems. 2. Impact of Weight on Quality Of Life-Lite (IWQOL-Lite) is a validated 31-item, self-report measure of obesity-specific quality of life. In addition to a total score, there are scores on five domains: physical function; self-esteem; sexual life; public distress; work.
Mental Health	HADS	The Hospital Anxiety and Depression Scale (HADS) comprises 14 items, 7 for anxiety, and 7 for depression. The scale yields individual anxiety and depression scores as well as an overall HADS score.
Physical Activity	1. IPAQ 2. SIT-Q-7D 3. ActiGraph GT3X	1. The International Physical Activity Questionnaire (IPAQ) comprises of seven questions recalling the previous week’s physical activity falling into four different physical activity domains: leisure-time activities, domestic and gardening activities, work-related activities, and transportation. 2. The Sedentary Behaviour Questionnaire (SIT-Q-7d) is a self-report recall measure of sedentariness over the last seven days. It assesses total daily sedentary time as an aggregate of sitting/lying down in five domains (meals, transportation, occupation, non-occupational screen time, and other sedentary time). 3. The ActiGraph GT3X is a wrist-worn activity monitor that uses triaxial accelerometry to collect physical activity and sleep data. Accerometry will be carried out over 7 consecutive days.
Energy Expenditure	Indirect calorimetry (Cosmed Fitmate GS)	Portable desktop indirect calorimeter for measurement of Resting Metabolic Rate (RMR)
Liver transient elastography	EchoSens Fibroscan 502 Touch	Non-invasive elastography device which gives 50 Hz shear wave speed measurements and estimates of liver stiffness as well as 3.5 MHz ultrasound coefficient of attenuation.

## Methods

DIADEM-I is an ongoing, non-blinded, randomised controlled, parallel-group trial examining the impact of an ILI using LED and physical activity for younger subjects with early T2DM.

The trial is registered with ISRCTN ISRCTN20754766 (date assigned: 7 June 2017), and ClinicalTrials.gov identifier (NCT03225339 (registered on 26 June 2017).). The description of the protocol is based on the latest version of the study protocol (DIADEM-I STUDY PROTOCOL v3–7 December 2016). The reported protocol follows the SPIRIT (Standard Protocol Items: Recommendations for Interventional Trials) recommendations (http://www.spirit-statement.org/). The SPIRIT checklist is provided in the Additional file 1. Figure 1 shows the CONSORT flow chart. Figure 2 shows the schedule of enrolment, intervention, study visits and assessments for the study groups.

**Fig. 1 Fig1:**
[figure not shown]
CONSORT flow chart for DIADEM-I Study. LED = Low Energy Diet; PA = Physical Activity

**Fig. 2 Fig2:**
[figure not shown]
Schedule of enrolment, intervention, study visits and assessments for both study groups

### Ethical approvals and monitoring

Ethical approval for the study has been obtained from the Weill Cornell Medicine – Qatar Institutional Review Board (IRB), Hamad Medical Corporation – Qatar IRB, Primary Health Care Corporation (PHCC) – Qatar IRB, and the Ministry of Public Health, Doha, Qatar. The study is supported by the Weill Cornell Medicine – Qatar institutional Data and Safety Monitoring Board (DSMB). Study monitoring will be conducted at 3-monthly intervals by the Clinical Research Core, Weill Cornell Medicine – Qatar following a standardised protocol.

### Study design

DIADEM-I is an open-label, pragmatic, parallel-group RCT, employing the following interventions (Fig. 2):Intensive Lifestyle Intervention (ILI) combining a low-energy diet (LED) approach with physical activity. Behavioural support for the lifestyle intervention will also be providedUsual medical care (UMC) aiming at diabetes education and support, and medical management of glycaemia, hypertension, and dyslipidaemia. This will be based on current clinical practice aiming to reduce diabetes symptoms and complications, and general recommendations on diet and physical activity.

### Description of Intensive Lifestyle Intervention (ILI)

The primary objective is for subjects to achieve a significant reduction in body weight at 12 weeks and continue progress at 1 year following a diet and physical activity ILI, and maintain this during the follow-up period. Diabetes remission will be assessed throughout the study.

#### Diet

Subjects are supported by a trained dietitian. The study will use a commercially available meal replacement plan – the Cambridge Weight Plan [51, 55, 75–78]. The ILI will use 800 kcal as a benchmark. For the first 12 weeks, subjects will be asked to consume mainly meal replacement products, supplemented by low-fat milk, to make total energy of approximately 800 kcal. Subjects will receive the meal replacement products, free of charge. If there is a need for additional snacks because of hunger, subjects will be recommended to eat raw vegetables and salad. For constipation, a common side effect, subjects will be recommended a fibre supplement (psyllium/inulin), if required. They will be advised to drink ≥2 l of water daily. From month 4 to month 6 inclusive, subjects will follow a partial meal replacement plan and will be introduced to normal solid foods providing daily energy-based on body weight as recommended in the Look AHEAD study. During the food introduction phase, focus will initially be on introducing protein-rich foods [79], skimmed milk, vegetables and salad. Then gradually, subjects will establish a three-meal-per-day eating pattern with support from the dietitian to help them identify appropriate acceptable foods (and portion sizes) to facilitate reintroduction of breakfast, lunch, and evening meal, and snacks. Recipes and meal plans will be provided and the emphasis will be on low-glycaemic-index foods. In the next 6 months, subjects will continue with lifestyle change and increasing physical activity. There will be a further 12-month follow-up period with subjects implementing lifestyle change. To aid self-monitoring, subjects will be provided with a personal activity device.

#### Physical activity

A fully trained exercise trainer will advise subjects in the activity arm to improve their fitness levels by engaging in unsupervised physical activity of at least 150 min per week. Previous studies have shown that at least 150 min of activity per week is effective for an impact on diabetes [66–68]. The planned ILI will follow the American College of Sports Medicine and American Diabetes Association position stand regarding physical activity [67]:Minimum of 150 min/week of exercise of at least moderate intensityAerobic exercise 3 days/week with no more than two consecutive days between boutsResistance exercise at least twice weekly on non-consecutive daysGradual rate of progression

The initial focus of activity is to reduce sedentariness, and encouragement of walking. For this reason, those unable to walk due to arthritis will be excluded. Walking activity will aim to achieve to at least 10,000 steps/day. As subjects progress, other aerobic activities and resistance training will be introduced. The objective is to introduce activities that are enjoyable to subjects, thus ensuring sustainability. Higher physical activity levels will be encouraged during the study for optimal weight loss, weight loss maintenance, and diabetes control. Increase in physical activity will be individualized based on progress. Potential benefits of variation in exercise activities will be pointed out [67].

#### Medications

It is aimed that diabetes medications will be discontinued with the adoption of LED. The process and rate of reduction of any medication will be judged clinically and will depend on symptoms, glycaemic control at baseline, and the subject’s motivation to adopt the LED. Blood pressure medications will be discontinued based on clinical assessments. For the UMC group, any medication intensification will aim to choose diabetes medications that either promote weight loss or are weight neutral.

#### Behavioural support

The behavioural aspects to support the dietary and activity intervention will be delivered by fully trained dietitians as well as physical activity trainers. These will be embedded within individual dietetic and activity appointments. Table 2 shows examples of the techniques employed in clinical weight management. The dietitians and physical activity trainers will follow a strict manual of procedures to cover all aspects of behaviour modification support including individualisation to address specific subject challenges and requirements. They will use specific presentations to ensure standardisation of delivery.

**Table 2 Tab2:** Behavioural support and self-management strategies [87] employed to support the lifestyle intervention in DIADEM-I

Behavioural support and self-management strategies	Examples of behavioural techniques
Self monitoring	• Identifying the relationship between mood and food selection and intake this will be accomplished using a food and mood diary • Using scales to gauge hunger and satiety • Regular weight measurement • Recording of food selection and intake
Goal setting	• SMART (Specific, Measureable, Achievable, Relevant and Time-Bound) goals will be used throughout • Individualised goals will be set by participants regarding diet and physical activity
Stimulus control	• Identification of external and internal triggers to unhealthy eating habits • Use of distraction techniques to help subjects avoid emotional eating
Cognitive restructuring	• Reviewing the impact of negative thoughts and beliefs and their impact on behaviour change. • Replacing negative thoughts and beliefs with positive thoughts and beliefs
Eating behaviour	• Education about healthy eating behaviours • Choosing low energy alternatives to high energy foods • Portion control • Timing and duration of eating • Dealing with snacking
Planning	• Planning meals and physical activity • Planning for challenging situations e.g. eating with family, eating at restaurants, and eating and activity while traveling
Maintenance	• Maintaining successful behaviours • Dealing with lapses and avoiding relapse • Avoiding previous behaviours that resulted in weight regain
Reward & support	• Non-food related rewards • Support from family and friends
Problem solving	• Problem solving skills • Dealing with high risk situations that impact on eating

#### Intervention duration and follow-up

The intervention will be for 12 months for the primary outcome measure with 12 months further follow-up.

The 2 study arms will have the following schedule:i.Intensive Lifestyle Intervention Group:InterventionPHASE 1: 12 weeks LED + physical activity;PHASE 2: 12 weeks partial LED + physical activity;PHASE 3: 6 months own food, physical activity, and lifestyle change.Follow-upd.PHASE 4: 12 months follow-up;e.PHASE 5: Post-study follow-up via electronic medical records (including body weight, medications, and biochemical measures).ii.Usual Medical Care Group:There will be 12 months usual care (optimising individualised glycaemic, blood pressure, and lipid control) with standard diet and activity advice, and a further 12 months follow-up. Contact frequency will be based on the current recommended usual care 3-monthly clinic attendance. To maintain participation in the study, the subjects in this group will receive regular monthly contact during the intervention from the research team via telephone and electronically in between formal visits.

#### Schedule of visits (ILI)

Table 3 shows the schedule of intervention visits for the ILI group.

**Table 3 Tab3:** Study phases and visit schedules for the intensive lifestyle intervention

Phase	Timeline	Individual Visit Schedule
1. Low Energy Diet + Physical Activity	Weeks 1–12	Visit every 2 weeks Dietitian (30 min/visit) Exercise trainer (30 min/visit)
		Physician review at baseline and on completion of Phase 1
2. Partial Low Energy Diet + Physical Activity	Weeks 13–24	Visit every 2 weeks Dietitian (30 min/visit) Exercise trainer (30 min/visit)
		Physician review on completion of Phase 2
3. Lifestyle change	Weeks 25–48	Visit every 4 weeks Dietitian (30 min/visit) Exercise trainer (30 min/visit)
		Physician review at 3-month and on completion of Phase 3
4. Follow-up	Weeks 49–96	3 monthly visits for follow-up Dietitian (30 min/visit) Exercise trainer (30 min/visit)
		Physician review at 3-month intervals and completion of Phase 4
5. Post Study	Minimum 2 years post-study	Review by weight management service Collection of data via electronic medical records

### Recruitment and Setting

The aim of the study is to assess the effectiveness of the ILI within the primary care setting. Research visits will occur in primary care, although usual care will be conducted either in the primary or secondary care setting depending on the participant’s diabetes care provider. Individuals will be identified, screened for eligibility and recruited from primary and secondary care in Qatar. Participants will be identified by their healthcare team in the outpatient department, and if they are interested in participating in the study, they will be scheduled for a screening visit. The referring clinician will ensure that all clinically routine blood and urine tests have been conducted to allow assessment of participant eligibility and participation. Informed consent is taken by a trained member of the research team independent of the referring physician.

### Eligibility criteria

The eligibility criteria are designed to include subjects appropriate for the study protocol. All relevant medical and non-medical conditions will be taken into consideration by the investigator team on whether the protocol is appropriate for an individual subject.

#### Inclusion criteria

The following inclusion criteria apply:Established physician diagnosed type 2 diabetes mellitus based on American Diabetes Association (ADA) criteria;Diabetes of ≤3-year duration;BMI > 27.0 kg/m^2^ (based on WHO cut-points for ethnicity [80]);Men and women;Age 18–50 years;Originating from the Middle East and North Africa region and resident in Qatar (to ensure diet homogeneity);Able to commit to the study duration;Able to give informed consent and willing to participate in the study.

#### Exclusion criteria

Subjects will not be eligible for enrolment in the study if they fulfil any of the following criteria:Type 1 diabetes mellitus based on clinical history;Cardiovascular event in the previous 6 months;Chronic kidney disease stage 3b or greater (estimated glomerular filtration rate eGFR < 30 mL/min/1.73 m^2^);Currently pregnant, lactating, or planning pregnancy within the study period;Any condition precipitating fluid overload such as heart failure (NYHA class > I) and liver cirrhosis;Significant previously diagnosed psychiatric disorder (e.g. schizophrenia, post-traumatic stress disorder, obsessive-compulsive disorder);Uncontrolled depression (based on hospital anxiety and depression scale);Uncontrolled epilepsy;Known lactose intolerance;Severe arthritis preventing walking;Active gout;Active gallstone disease or known asymptomatic gallstones.

These exclusion criteria also include conditions that may be affected by use and composition of a low energy meal replacement diet e.g. lactose intolerance. Cardiovascular events are ischaemia-related events (e.g. myocardial infarction, angina, transient ischaemic attack, and stroke).

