### Subject adherence, withdrawal, safety measures and adverse events

Adherence will be measured at each visit. Subjects will be asked about their dietary intake and physical activity. Subjects in the ILI will be asked to return any empty packets or unused meal replacement products to examine usage. Subjects who are found to be non-adherent or withdraw in the first 6 weeks of the study will be replaced.

The subject has the right to withdraw their consent anytime without giving any reason. The subject’s reason for withdrawal (if reported) will be recorded. Subjects will be notified that if they choose to withdraw from the study, the investigative team will not proceed with further assessments and data collection but their previously collected data will be used for research purposes. Withdrawal from the study will be recorded in the electronic medical record.

Also, the study will withdraw the subject if:The subject is unable to adhere to the study protocol and study requirements;There is a significant protocol deviation;The subject becomes pregnant during the study;Any new illness that affects their inclusion (exclusion criteria above);Continuing in the study is deemed harmful to the subject’s health;The subject is lost to follow up;The trial cancels.

All female subjects will be asked to report if they miss any menstrual cycle. A urine pregnancy test will be conducted and subjects withdrawn if the test is positive.

Any harm that may result in a subject’s withdrawal, or is present at the end of the study, will be followed up until a satisfactory resolution occurs. Safety measures include home capillary blood glucose monitoring (for hyper- and hypoglycaemia), blood pressure measures, electrocardiogram at baseline (to identify any covert cardiac disease that may affect physical activity), and laboratory measures to assess any blood, liver, renal, or nutritional abnormalities. Specific advice will be given regarding home blood glucose monitoring for hypo- and hyper- glycaemia, as well as other foreseeable changes associated with weight loss or dietary change and increased activity. Medications that may increase risk of adverse effects will be discontinued.

All adverse events (AE) will be collected and reported using specific forms. At every visit, the subject will be asked about any experiences by asking: “since your last visit, have you experienced any problems?” All AEs will be recorded and evaluated by the Investigators.

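### The kidney exclusion contradicts itself: stage 3b or greater means eGFR below 45, but the criterion gives eGFR below 30

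*Protocol article*

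**What the plan says.** The renal criterion is a single line in the Exclusion criteria of the protocol article. It names a stage and opens a bracket to explain it, "Chronic kidney disease stage 3b or greater (estimated glomerular filtration rate eGFR", and the bracket in full reads "estimated glomerular filtration rate eGFR < 30 mL/min/1.73 m^2".

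The list is binding, and one criterion is enough to exclude: "Subjects will not be eligible for enrolment in the study if they fulfil any of the following criteria".

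Two other places bear on how the line works:

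- Eligibility criteria gives the team general latitude: "All relevant medical and non-medical conditions will be taken into consideration by the investigator team". No renal threshold is attached to it.
- The section on subject adherence, withdrawal, safety measures and adverse events applies the exclusion list again after enrolment. One ground for withdrawal is "Any new illness that affects their inclusion (exclusion criteria above").

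No other part of the article gives an eGFR cut-off, defines the kidney disease stages, or says whether the stage or the number takes precedence. The abbreviation list only spells out CKD and eGFR.

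**The concern.** The bracket should restate the stage as a laboratory value, but it gives the limit of a more severe stage. A screener who works from a recorded diagnosis of stage 3b excludes the patient. A screener who works from an eGFR of 38 on the laboratory report does not. Both have followed the sentence.

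The limit has a protective purpose. The intervention is roughly 800 kcal a day for 12 weeks, mainly from meal replacements, with a daily fluid target and withdrawal of diabetes and blood pressure drugs. The article itself says that the exclusions include conditions the diet might affect. Participants come from both primary and secondary care, and eligibility is judged partly from routine blood and urine tests, so different people could apply different halves of the line.

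Three things are at stake:

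- who may safely start the diet;
- whether an enrolled person with eGFR 30–44 counts as an eligibility violation, which could affect the planned per-protocol analyses;
- whether a participant whose kidney function declines is withdrawn or kept.

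Nephropathy is also among the secondary outcomes, so the renal range admitted has some bearing there.

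**Working it through.** No sample-size or power formula applies. The check is whether the stage and the number select the same patients.

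**Inputs**

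- Stage label: 3b or greater (Exclusion criteria).
- Numeric limit: eGFR below 30 mL/min/1.73 m² (same line).
- Stage boundaries: G3a 45–59, G3b 30–44, G4 15–29, G5 below 15 mL/min/1.73 m². The article does not print these. They are taken as the fixed meaning of the staging term it uses.

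**Translating each half**

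- Label: 3b or greater = G3b + G4 + G5 = eGFR below 45.
- Number: eGFR below 30 = G4 + G5 = stage 4 or greater.

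The printed limit of 30 is therefore not reproduced from the printed stage, which gives 45.

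**Side by side, for a person with established chronic kidney disease**

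| eGFR (mL/min/1.73 m²) | Stage | By the label | By the number |
|---|---|---|---|
| 45–59 | 3a | not excluded | not excluded |
| 30–44 | 3b | **excluded** | **not excluded** |
| 15–29 | 4 | excluded | excluded |
| below 15 | 5 | excluded | excluded |

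The two halves disagree in exactly one band, from 30 to just under 45, a width of 45 − 30 = 15 units. They agree everywhere else.

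**Does anything else settle it?** The investigator's general judgement can keep an unsuitable person out, but it does not say which half of this criterion is the rule. The withdrawal section refers back to the same list and so inherits the mismatch: a participant whose eGFR falls to 40 through new kidney disease meets the criterion by the label and does not meet it by the number.

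**How many people?** The article gives no eGFR distribution, so no count can be derived. The entry limits "Age 18–50 years" and "Diabetes of ≤3-year duration" suggest that few will fall in the band. For scale, each such participant would be 1/138 = 0.7% of the planned total of 138.

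**Sample size.** The stated inputs are a 7% difference in weight loss, an SD of 9%, power 0.8, significance level 0.05 and 30% inflation for dropout. None depends on the renal criterion, so 69 per group is unaffected.

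**The case against.** The best case on the other side accepts the mismatch and disputes its weight.

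- **Few patients, no bias.** In this age range and with such recent diabetes, eGFR 30–44 should be uncommon. Eligibility is settled before allocation, so uneven screening would not favour either arm. This stands for entry to the trial. It does not cover the reuse of the criterion for withdrawal, which happens after randomisation in an open-label study.
- **Other safeguards.** Routine tests precede the eligibility decision, the investigators weigh all relevant conditions, renal laboratory measures are part of safety monitoring, a participant can be withdrawn if continuing is judged harmful, and medication reduction is a clinical decision. A person with eGFR 38 would not pass unexamined. This also stands and limits the risk, but none of these safeguards supplies a renal cut-off.
- **No evidence of harm in the band.** Nothing in the article shows that eGFR 30–44 is unsafe on this diet. That is correct, and it is why the choice of cut-off belongs to the clinical team.
- **Possibly a slip in the article only.** The article describes version 3 of the protocol, dated 7 December 2016, which is not shown, and neither is the screening form. The working documents may be right. This affects where the correction has to be made, but the published criterion is still wrong as it reads.

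**Conclusion.** The criterion is wrong as written. The stage and the number cannot both be the rule, and for people with chronic kidney disease and eGFR 30–44 they give opposite answers.

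The practical effect is probably small: a 15-unit band, an unknown but likely low number of people, and no change to the sample size or the primary analysis model. No bias in the 12-month weight comparison is claimed. The correction is still worth making, because this is an operative safety threshold that is used at entry and again for withdrawal.

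The conclusion rests on one assumption from outside the document, the standard stage boundaries. Whether anyone was actually screened inconsistently cannot be told from the article.

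**What to change.** 1. Check protocol version 3 and the screening form to see which limit they carry.
2. Have the clinical team decide which was intended, then print one matched pair. If the stage governs, write stage 3b or greater with eGFR below 45 mL/min/1.73 m². If the number governs, write stage 4 or greater with eGFR below 30 mL/min/1.73 m².
3. Use the same wording in the protocol, the screening form and the withdrawal rule, and record the change in the trial registries, as the article undertakes to do for amendments.
4. List the screening eGFR of everyone enrolled, identify any value from 30 to just under 45, and handle those cases under the corrected rule. If the limit becomes 45, decide how they are treated in the per-protocol population before outcomes are compared.

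The cost is a one-line correction and a look through screening data that should already be on file. The sample size and the primary analysis do not change.
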